#### Recruitment and Data Collection

Households will be randomly sampled from selected communities in both the control and intervention arms and 1 eligible child recruited at random in each household. A short baseline questionnaire will be administered to collect individual data on each child and to confirm their eligibility after the caregivers provided their consent. In the intervention arm, the questionnaire will be administered before the intake of SPAQ for SMC. The primary end point will be recorded through passive surveillance by study clinicians in both the intervention and comparator areas during the 4-month study period. Children recruited into the study presenting at clinics will be identified using information on SMC record cards, on which a child’s information and SMC doses are recorded, and data on health facility visits including suspected malaria cases and results of RDTs will be matched to baseline questionnaire data to build a database for analysis.

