### Study Design

We will adopt a type 2 hybrid effectiveness-implementation study design that evaluates the effects of a clinical intervention on relevant outcomes while collecting information on implementation [29]. The hybrid effectiveness-implementation study design supports the pursuit of different lines of research simultaneously, which facilitates the more rapid translation and uptake of study findings for policy makers and implementers [29,30]. This study will use mixed methods to address the aforementioned objectives. Assessments of the protective effect of SPAQ, as delivered as part of SMC implementation, will provide evidence on whether this is appropriate in a region where SP resistance is suspected. Evaluating the implementation of SMC will generate knowledge on the feasibility and acceptability of this intervention in situ, including the challenges, barriers, and facilitators in the local context. Such findings can be useful to inform which intervention components are generalizable and which require local adaptation for other settings [31].

Four monthly cycles of SMC drugs will be distributed door-to-door to eligible children aged between 3 and 59 months by community distributors between November 2020 and February 2021 in 2 districts of Nampula Province. SMC tools and protocols used in Sahelian countries where the Malaria Consortium supports SMC delivery will be adapted to the context in Mozambique for this purpose. A third district will serve as a comparison district (the latter will receive standard malaria prevention, control, and case management). Data collection across the study components was conducted between October 2020 and May 2021 (Figure 3).

The methods are organized according to the study objective, described in more detail below, with an overview provided in Table 2 and Figure 3.

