### Nonrandomized Controlled Trial

#### Overview

A nonrandomized controlled trial will be conducted to determine whether the receipt of SPAQ is associated with a reduction in the odds of clinically significant malaria outcomes and to estimate the protective effect of SPAQ. There will be two arms: one (control arm) in the comparator district and the other in one of the SMC intervention districts. Communities will be randomly selected in both the intervention and control districts. Eligible children (aged 3-59 months at the first SMC cycle) will be recruited through random selection. Exclusion criteria include the presence of a severe, chronic illness and a history of a significant adverse reaction to SP or AQ. Selected children will be treated appropriately and retained during the trial. In the control district, communities bordering the intervention district will be avoided because of potential unintended *leakage* of SPAQ across the district boundary.

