#### Primary Outcome

The primary outcome of this study will be visits to a health facility for suspected malaria by eligible children and confirmation of malaria diagnosis using an RDT during the 5-month study period, which includes a period of 28 days after the final administration of SPAQ.

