#### Data Analysis

Data will be analyzed using multivariate logistic regression with odds ratios estimated for the association between allocation to the intervention arm and (suspected and confirmed) malaria diagnosis at any point during the study period, converted to a percentage estimate of protective effect. To compensate for the lack of preintervention random allocation of participants to intervention or control groups, covariate adjustment will be made for potential confounders that may influence respondents’ odds of experiencing a clinically significant case of malaria. Covariates, measured at baseline, will include sex, age, parental education, and long-lasting insecticidal net use and all of these will be operationalized as categorical variables. Analyses will also use a multivariate Cox proportional hazards model with multiple Cox regression. *Failure* defined as a visit to a health facility for suspected malaria and/or a confirmed case of malaria and timing of this event based on the original date of health facility attendance during the study period and the estimated protective effect calculated.

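### Trial children are identified at clinics by SMC record cards, but the control district has no SMC and no identifier is named for control children, so linkage of the primary outcome may differ by arm

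*Protocol article*

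**What the plan says.** All references are to the protocol article.

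- **Where SMC is given.** Under Study Design, drugs are distributed door to door "by community distributors between November 2020 and February 2021 in 2 districts of Nampula Province". Of the third district the article says that "the latter will receive standard malaria prevention, control, and case management".
- **Where the arms are.** The trial's Overview places "one (control arm) in the comparator district and the other in one of the SMC intervention districts".
- **Outcome.** The Primary Outcome section defines it as "visits to a health facility for suspected malaria by eligible children and confirmation of malaria diagnosis using an RDT".
- **Surveillance.** Under Recruitment and Data Collection, "The primary end point will be recorded through passive surveillance by study clinicians in both the intervention and comparator areas".
- **Identification.** The same section continues: "Children recruited into the study presenting at clinics will be identified using information on SMC record cards". It describes the card as holding the child's details and SMC doses.
- **Linkage.** Facility visit data and "results of RDTs will be matched to baseline questionnaire data to build a database for analysis".
- **Analysis.** Under Data Analysis, logistic regression gives "odds ratios estimated for the association between allocation to the intervention arm and (suspected and confirmed) malaria diagnosis" at any time in the study, and the odds ratio is converted to a percentage protective effect. A Cox model uses the date of attendance.

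**The concern.** The identification rule is written for all recruited children, yet the identifier belongs to a programme that only one arm receives. In the SMC arm, distributors visit each month and the card is part of delivery. In the control arm nothing in the article produces or maintains such a card.

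The article describes no active follow-up of trial children. If none of a child's malaria visits is linked, that child enters the logistic model as a non-case, and the Cox model misses the failure. Lower linkage in one arm is therefore differential misclassification of the primary outcome. The planned covariates (sex, age, parental education, net use) do not measure linkage and cannot correct for it, and a larger sample would not remove it.

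This component estimates the protective effect of the drug combination, one of the two primary aims, in an area where resistance is expected to be high. A weak or null estimate caused by missed control cases could be read as failure of the drugs through resistance.

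**Working it through.** **Inputs from the Sample Size section.** Control risk 0.20 per season; 40% reduction, so 0.12 under SMC; 5% level; 80% power; 327 per arm (654 in total); 818 after 20% attrition; recruitment target 400 per arm.

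**Reproducing the plan's figure.** Unpooled two-proportion formula, two-sided:

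n = (1.960 + 0.842)² × (0.20×0.80 + 0.12×0.88) / (0.20 − 0.12)² = 7.849 × 0.2656 / 0.0064 = 325.7, so 326 per arm.

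The pooled formula gives 329. The stated 327 lies between them, and 654 / 0.80 = 817.5, so 818. The sample size itself is not in question.

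**Assumption.** Let s_C and s_I be the shares of children with malaria in the control and SMC arms who have at least one malaria visit linked. The article gives no value for either, so every value below is illustrative.

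**Formulas.**
- Observed risks: 0.20·s_C and 0.12·s_I.
- Observed risk ratio: 0.60 × s_I / s_C.
- Observed odds ratio: computed from the two observed risks. This is the scale from which the plan takes its protective effect.
- Power: unpooled two-sided z test with 400 × 0.80 = 320 per arm.

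Worked case, s_C = 0.90 and s_I = 1:
- Control risk 0.18.
- Odds ratio (0.12/0.88) / (0.18/0.82) = 0.1364 / 0.2195 = 0.621, so protective effect 37.9%.
- Standard error √[(0.1476 + 0.1056)/320] = 0.0281; z = 0.06 / 0.0281 = 2.13; power = Φ(2.13 − 1.96) = 57%.

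**Control linkage varied, SMC-arm linkage 100%:**

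| Control linkage | Observed control risk | Effect, risk scale | Effect, odds scale | Power |
|---|---|---|---|---|
| 100% | 0.20 | 40% | 45.5% | 79% |
| 90% | 0.18 | 33% | 37.9% | 57% |
| 80% | 0.16 | 25% | 28.4% | 31% |
| 60% | 0.12 | 0% | 0% | not applicable |
| 50% | 0.10 | −20% | −22.7% | not applicable |

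**Incomplete linkage in both arms:**
- 80% in each arm: risks 0.16 and 0.096; risk ratio still 0.60; protective effect on the odds scale 44.2% instead of 45.5%.
- 80% in the SMC arm and 60% in the control arm: risks 0.12 and 0.096; protective effect 20% (risk) and 22.1% (odds).
- 80% in the SMC arm and 100% in the control arm: risks 0.20 and 0.096; protective effect 52% (risk) and 57.5% (odds). The bias reverses if the SMC arm is the worse linked.

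The harm thus comes from the ratio of linkage between arms, not from incompleteness as such. With a true risk ratio of 0.60, the observed effect vanishes when control linkage is 60% of SMC-arm linkage.

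**The case against.** The strongest reply is that nothing in the article says control children lack cards. Surveillance is stated for both areas, and the identification sentence covers recruited children without limiting it to one arm. Read literally, control children might carry a card with empty dose fields, handed out at the baseline visit. Study clinicians do the surveillance in both areas, and visits are matched to baseline questionnaire data. The matching fields are not listed, so the card may not be indispensable. The full protocol and data collection tools exist separately and may settle who issues what.

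Much of this stands. A reader might infer that control children cannot be identified at all, or that control cases are certain to be missed. The documents do not support either reading: they neither deny control children a card nor show that matching fails without one. A near-total failure would also leave almost no control events and be noticed. Nor do the linkage shares in the working come from the plan, and full linkage in the SMC arm is a favourable assumption, since caregivers may not bring cards to the clinic.

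What does not stand is that this is only detail left out of a condensed article. The article states a mechanism, and that mechanism uses a programme dose card in a district without the programme. It gives no sign that the card, or a substitute, is issued there.

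**Conclusion.** The concern holds as a conditional one. The only identifier named for trial children does not fit the control arm as the article describes it. Unless control children receive an equivalent card, linkage is likely to be lower there, and the protective effect would be biased toward the null or apparent harm. That direction assumes linkage is at least as good in the SMC arm.

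The actual size is unknown. If the gap is 10 percentage points with full SMC-arm linkage, power falls by about 22 points; a 20-point gap leaves less than half the planned power. If linkage is equal, even if incomplete, the risk ratio is unbiased and the odds ratio nearly so. Equal ascertainment is a precondition for interpreting this comparison and has to be shown.

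**What to change.** At the baseline visit, which already takes place in both arms:

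1. Issue the same study ID card to every enrolled child in both arms, with study number, name, date of birth and community, and no dose record.
2. Match facility visits to the enrolment list on the same identifiers and by the same procedure in both arms, whether or not a card is shown.
3. Use the SMC card only for dose history.
4. Report the linked share by arm with the primary result.

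The abstract says that data collection began in October 2020. If enrolment is already complete, state how control children were identified, apply step 2 retrospectively to both arms where the facility records allow it, and report step 4.

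Cost: about 800 printed cards, a sentence or two in the procedures, and some extra matching work. Sample size and analysis model are unchanged.

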#### Data Analysis

Data will be analyzed using multivariate logistic regression with odds ratios estimated for the association between allocation to the intervention arm and (suspected and confirmed) malaria diagnosis at any point during the study period, converted to a percentage estimate of protective effect. To compensate for the lack of preintervention random allocation of participants to intervention or control groups, covariate adjustment will be made for potential confounders that may influence respondents’ odds of experiencing a clinically significant case of malaria. Covariates, measured at baseline, will include sex, age, parental education, and long-lasting insecticidal net use and all of these will be operationalized as categorical variables. Analyses will also use a multivariate Cox proportional hazards model with multiple Cox regression. *Failure* defined as a visit to a health facility for suspected malaria and/or a confirmed case of malaria and timing of this event based on the original date of health facility attendance during the study period and the estimated protective effect calculated.

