#### Sample Size

The study will be powered to have an 80% chance of detecting a 40% reduction in incidence with statistical significance at the 5% level. It is assumed that study participants, in the absence of SMC, would experience 0.2 clinical episodes per child per high-transmission season (corresponding to the SMC round) of sufficient severity to present to a health facility [10]. The sample size calculation, based on the formula for a binary outcome superiority trial, shows that a sample of 654 eligible children (or 327 per arm) is required to provide sufficient statistical power. This multiplies to 818 under the assumption of a 20% loss to follow-up over the four cycles. Therefore, we aim to recruit a minimum of 800 eligible children (400 per arm).

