#### Sample Size and Technique

The end-of-round survey will use multistage random samples of households in areas covered by the Malaria Consortium’s SMC pilot and will intend to achieve a representative sample of the target population at the district level to estimate the coverage of SMC at the level of individual eligible children. The sampling protocol aims to achieve a self-weighted sample with sampling units selected with a probability proportional to size. Only at the last stage of sampling (ie, at the household level) will a constant number of eligible children (1 child per household) be selected. The survey will be powered to provide an estimate of SMC coverage for children aged 3-59 months with a margin of error of 5%, while also providing a representative sample of children aged 60-119 months. The main sampling frame for the selection process will be a list of villages. Villages will then be randomly selected using the probability proportional to size. Villages will be the primary unit of sampling through which households and eligible children will be selected randomly. This may be reviewed once the study starts if this approach is not feasible in practice. A primary caregiver in this survey refers to any individual, aged at least 18 years, with the primary responsibility of feeding and daily care of at least one child aged less than 5 years, in a household where he or she has been a resident before the start of the SMC pilot or 1 month before the last cycle of SMC. The sample size calculation was performed using Stata 16 using the *svysampsi* command, based on the following assumptions: (1) the assumed intracluster correlation is 0.2; (2) 15 eligible children per cluster (b=cluster size); (3) the (design/cluster effect) = 1 + (b − 1) intracluster correlation = 1 + (15 − 1) 0.2 = 3.8; (4) the coverage rate of SMC in children aged 0-4 years of at least 80% (and in children aged 5-9 years of at most 20%); (5) a margin of error of 5%; (6) finite population adjustment is applied (75,000); (7) nonresponse rate of 5%; and (8) assumed ratio of children aged 5-9 years to those aged 0-4 years of 0.88.

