#### Data Analysis

Data analysis will be carried out using Stata 16. Coverage will be calculated using the proportion command. Population size weights will be applied using the svy command as appropriate for estimates of coverage indicators when it is not possible to achieve a self-weighting sample. All indicators of interest will be calculated as proportions by district and an average across both districts.

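### The nonrandomized trial samples children within communities, but its sample size has no design effect and its models, as written, name no provision for clustering, so the stated 80% power is not a property of this design

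*Protocol article*

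**What the plan says.** All references are to the protocol article, under Nonrandomized Controlled Trial unless another section is named.

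- **Design (Overview; Recruitment and Data Collection).** There are two arms, each located in a single district. On the first sampling stage the article says: "Communities will be randomly selected in both the intervention and control districts". Sampling then moves to households inside the chosen communities, with one eligible child taken per household. The number of communities is not given.
- **Sample size (Sample Size).** The aim is worded "The study will be powered to have an 80% chance of detecting a 40% reduction in incidence"; the significance level is 5%. The control-arm assumption is that, without the intervention, children "would experience 0.2 clinical episodes per child per high-transmission season". The result is reported thus: "The sample size calculation, based on the formula for a binary outcome superiority trial, shows that a sample of 654 eligible children". Half of that number, 327, falls in each arm. Allowing for 20% loss gives 818, and the recruitment target is then set at a minimum of 800 (400 per arm). No other inflation is mentioned.
- **Models (Data Analysis).** The main model is described as follows: "Data will be analyzed using multivariate logistic regression with odds ratios estimated for the association between allocation to the intervention arm". Its outcome is a malaria diagnosis, and a Cox model is added. The covariates are sex, age, parental education and net use, all measured on the child or family. No community term, random effect, frailty or cluster-robust variance is named.

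**The concern.** The primary outcome is a health-facility visit for suspected malaria with a positive rapid test. It depends on local transmission and on access to a facility, and children in one community share both. Taking one child per household removes household clustering but leaves community clustering in place. If outcomes within communities are positively correlated, 320 children per arm carry less information than 320 independent children.

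Two things follow. The power claim rests on a variance that is too small. A standard logistic or Cox fit also understates the uncertainty of the protective effect. The trial serves one of the study's two primary aims, in a setting where resistance to sulfadoxine-pyrimethamine is expected to be high. Intervals that are too narrow could present chance differences between communities as protection. Low power could let a null result be read as failure of the intervention.

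**Working it through.** **Inputs from Sample Size:** control proportion 0.20; 40% reduction, so 0.12; 5% level (two-sided is not stated but fits the article's figure); 80% power; 20% loss; 400 recruited per arm.

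**Step 1: reproduce the stated figure.** Variance sum: 0.20 × 0.80 + 0.12 × 0.88 = 0.2656. Unpooled formula: n = (1.96 + 0.842)² × 0.2656 / 0.08² = 7.849 × 0.2656 / 0.0064 = 325.7, so 326 per arm. The pooled version gives 329. The stated 327 lies between them; a continuity-corrected formula (354) and a one-sided one (259) do not fit. For loss, 654 / 0.8 = 817.5, so 818. The stated figure therefore contains a design effect of 1.

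**Step 2: power at the actual target.** 400 × 0.8 = 320 evaluable per arm. Standard error = √(0.2656 / 320) = 0.0288; 0.08 / 0.0288 = 2.777; power = Φ(2.777 − 1.96) = 79.3% (79.0% pooled). No reserve is left for clustering.

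**Step 3: add clustering.** The number of evaluable children per community (m) and the ICC are assumptions, because the article gives neither for this trial. Formulas:

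- design effect DE = 1 + (m − 1) × ICC
- effective sample size per arm = 320 / DE
- power = Φ(0.08 / √(0.2656 × DE / 320) − 1.96)
- correct interval width relative to the naive one = √DE
- type I error of an unadjusted 5% test = 2 × (1 − Φ(1.96 / √DE))

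| m | ICC | DE | Effective n per arm | Power | Width ratio | Type I error, unadjusted |
|---|---|---|---|---|---|---|
| 3 | 0.01 | 1.02 | 313.7 | 78.5% | 1.01 | 5% |
| 3 | 0.05 | 1.10 | 290.9 | 75.4% | 1.05 | 6% |
| 5 | 0.01 | 1.04 | 307.7 | 77.7% | 1.02 | 5% |
| 5 | 0.05 | 1.20 | 266.7 | 71.7% | 1.10 | 7% |
| 10 | 0.01 | 1.09 | 293.6 | 75.8% | 1.04 | 6% |
| 10 | 0.05 | 1.45 | 220.7 | 63.5% | 1.20 | 10% |
| 20 | 0.01 | 1.19 | 268.9 | 72.1% | 1.09 | 7% |
| 20 | 0.05 | 1.95 | 164.1 | 51.1% | 1.40 | 16% |

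The power column is for a test that allows for clustering. The type I error column counts community clustering only, not any difference between the two districts.

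**Step 4: what 80% power would need.** Total recruited = 2 × (327 × DE) / 0.8, with each arm rounded up. At DE 1.02: 334 per arm, 668 / 0.8 = 835. At DE 1.95: 638 per arm, 1276 / 0.8 = 1595. Both exceed 800.

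**The case against.** **The models.** The Data Analysis text lists models and covariates but does not say that children are treated as independent. A cluster-robust variance is compatible with it, and the choice of standard error is often left to an analysis plan, which is not shown here. This stands to the extent that a reader should not infer a stated decision to ignore clustering. What can be said is that the models as written carry no such provision, and that run that way their intervals would be too narrow. The argument does not reach the sample size: an analysis plan could correct the intervals, but it could not make the stated 80% power true at the same number of children.

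**The size.** With many communities and few children in each, the loss is modest: 3 to 5 children per community gives about 79% to 72% power. This stands, and the range above includes it. The 51% is the unfavourable corner, not an expected value.

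**The coverage survey's ICC.** A reader might take that survey's planning value ("the assumed intracluster correlation is 0.2") as the article's own figure for this trial. The documents do not support that: it concerns receipt of chemoprevention, not malaria visits. No power figure here uses it.

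**The coverage survey's analysis.** A reader might also infer from "Coverage will be calculated using the proportion command. Population size weights will be applied using the svy command as appropriate" that villages would be ignored whenever the sample is self-weighting. The sentence says when weights apply, not how variance is estimated, and that survey is sized with a design effect of 3.8. The point is therefore confined to the nonrandomized trial.

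**Conclusion.** The concern holds for the nonrandomized trial. That the sample size makes no allowance for clustering is shown by reproduction and needs no assumption. That 80% power is not reached for any positive ICC follows directly, since the target gives about 79% even at an ICC of zero. That the intervals would be too narrow is conditional on the models being run as written.

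The direction is certain for any positive ICC, but the size is not. Over 3 to 20 evaluable children per community and an ICC of 0.01 to 0.05, power runs from about 79% to 51%, unadjusted type I error from about 5% to 16%, and correct intervals are 1.01 to 1.40 times as wide as unadjusted ones.

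A reader might also infer that a community-level adjustment would make the comparison fully valid. It would not. With one district per arm, any district difference is inseparable from the intervention effect, and no model on these data can put between-district variation into the interval.

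**What to change.** 1. **Data Analysis:** fit both models with community as the cluster. Use a community random effect in the logistic model and a shared frailty in the Cox model, or cluster-robust variance with a small-sample correction in both. The correction matters if communities are few: 20 evaluable children per community would mean only 320 / 20 = 16 communities per arm.
2. **Sample Size:** restate the power for the planned 800 children, giving the number of communities, the children per community, a justified ICC range and the resulting design effect.
3. **Data Analysis or Limitations:** state that with one district per arm the interval reflects sampling within the two districts only and cannot include between-district variation.

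The cost is wider intervals and a less favourable stated power. No new data are needed, but these changes disclose the lower power and do not restore 80%. Restoring it would take about 835 to 1595 recruits under the assumptions above, and the article reports that data collection began in October 2020.

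### The plan does not say how the odds ratio becomes a percentage protective effect; under the usual 1 − OR, a true 40% reduction would be reported as about 42% to 45%, and the Cox estimate carries the same label

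*Protocol article*

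**What the plan says.** All references are to the Protocol article, under Nonrandomized Controlled Trial unless stated otherwise.

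- **Data Analysis.** Logistic regression, adjusted for baseline covariates, gives an odds ratio comparing the arms on "malaria diagnosis at any point during the study period, converted to a percentage estimate of protective effect". No conversion formula is given. A risk ratio, standardised risks and a rare-outcome argument are not mentioned. The same paragraph plans a multivariable Cox model, from which a protective effect is also to be calculated. It does not say which of the two is the main result.
- **Sample Size.** "The study will be powered to have an 80% chance of detecting a 40% reduction in incidence". The starting point is on an episode scale: "It is assumed that study participants, in the absence of SMC, would experience 0.2 clinical episodes per child per high-transmission season". The calculation is nevertheless "based on the formula for a binary outcome superiority trial".
- **Overview, and objective 2 in Study Aims.** The question is worded as a reduction in the odds of clinically significant malaria. The Overview adds that the protective effect of SPAQ is to be estimated.
- **Recruitment and Data Collection.** Children are enrolled at baseline and followed forward through passive surveillance, so each arm has a known denominator.

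**The concern.** Enrolled children are followed forward, so risks and rates can be estimated directly and an odds ratio is not forced by the design. When the outcome is not rare and the intervention protects, 1 − OR is always larger than 1 − RR. At the protocol's own control risk of about 20%, the gap is visible in the reported figure.

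The protective effect of SPAQ is one of the two primary aims. Readers will naturally set the percentage beside the 40% used for planning and the roughly 75% reduction in clinical episodes cited in the Introduction. A figure on the odds scale is not comparable with either, and it errs in the less cautious direction in a setting where SP resistance is expected to be high. A second figure from the Cox model under the same name leaves it unclear which quantity is meant.

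**Working it through.** **Inputs from the Sample Size section.** Control value 0.2; 40% reduction, hence 0.2 × 0.6 = 0.12; power 80%; significance level 5%, with sidedness not stated; 327 per arm; 20% loss to follow-up.

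**Assumption.** The conversion is (1 − OR) × 100. This is the usual reading, but it is not written in the article.

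**1. Reproduce the plan's sample size.** With two proportions, unpooled variance and a two-sided 5% level:

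n = (1.960 + 0.842)² × (0.20 × 0.80 + 0.12 × 0.88) / (0.20 − 0.12)² = 325.7, so 326 per arm.

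The pooled-variance form gives 329. Both agree closely with "a sample of 654 eligible children (or 327 per arm) is required". A one-sided test gives 259 and a continuity correction gives 354, and neither matches. For losses, 654 / 0.8 = 817.5, which rounds to the stated 818. The trial is therefore sized on risks of 0.20 and 0.12, a risk ratio of 0.60.

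**2. The same effect as 1 − OR.**

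OR = (0.12/0.88) / (0.20/0.80) = 0.1364 / 0.25 = 0.545, so 1 − OR = 45.5%.

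The true risk reduction is 40.0%, a gap of 5.5 percentage points.

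**3. The reverse direction.** If 40% is reported because OR = 0.60, the odds under SMC are 0.60 × 0.25 = 0.15 and the risk is 0.15/1.15 = 0.130. The true risk reduction is then 1 − 0.130/0.20 = 34.8%.

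**4. If 0.2 and 0.12 are episode rates (Poisson).** The risks of at least one episode are 1 − e^(−0.2) = 0.181 and 1 − e^(−0.12) = 0.113.

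- OR = (0.113/0.887) / (0.181/0.819) = 0.576, so 1 − OR = 42.4%.
- The rate reduction is 40%, a gap of 2.4 points.
- The risk reduction is 37.6%, a gap of 4.8 points.

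**5. The Cox quantity at the design risks.** With proportional hazards, HR = ln(0.88)/ln(0.80) = 0.573, so 1 − HR = 42.7%. This lies 45.5 − 42.7 = 2.8 points below 1 − OR for the same children.

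**6. Sensitivity to the control risk, which is an assumption.** For a true risk reduction of 40%:

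| Control risk | 1 − OR |
|---|---|
| 10% | 42.6% |
| 15% | 44.0% |
| 20% | 45.5% |
| 25% | 47.1% |
| 30% | 48.8% |

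The direction never changes.

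**7. Scale against sampling error.** At 327 per arm, the expected numbers with and without the event are 65.4 and 261.6 (control) and 39.24 and 287.76 (SMC).

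SE(log OR) = √(1/65.4 + 1/261.6 + 1/39.24 + 1/287.76) = 0.219.

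The unadjusted 95% interval for the OR is 0.545 × e^(±1.96 × 0.219), or 0.355 to 0.838. On the 1 − OR scale that is about 16% to 65%.

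**The case against.** Four objections carry weight.

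- **The formula is not in the text.** A reader might infer that the plan commits to 1 − OR and that the published figure will certainly be too high. The document does not say so. It states only that a conversion is made, and converting the odds ratio to a risk ratio at the control risk would remove the bias: 0.545 / (1 − 0.20 + 0.20 × 0.545) = 0.60. A fuller study protocol exists, according to Availability of Data and Materials, and may give the formula. This stands, and the conclusion is conditional on it.
- **The objective is worded in odds.** Logistic regression answers that objective as written. This supports reporting an odds ratio. It does not support presenting 1 − OR as a protective effect in a trial sized on incidence.
- **The Cox model is already planned.** An estimate closer to the incidence scale will therefore be available. What remains open is which figure is the protective effect.
- **The gap is modest.** It is 2.4 to 5.5 points, against an interval running from about 16% to 65%. That is a fair comparison. Sampling error does not lean one way, however, and this gap does.

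Two further inferences would go too far. First, not every effect cited in the Introduction is a reduction in incidence, since the 88% figure comes from case-control studies. Second, a much larger overstatement would need a control risk well above 20%, for which the documents give no figure. The Data Analysis wording also mentions suspected malaria, and counting suspected visits could raise the risk, but by an unknown amount.

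**Conclusion.** The point holds in conditional form. If the conversion is (1 − OR) × 100, a true 40% reduction would be reported as about 45.5% at the design risks, or about 42.4% if the inputs are episode rates. The overstatement is 5.5 points against the risk reduction in the first case and 2.4 points against the rate reduction in the second. Independently of the formula, the logistic and Cox models give different quantities under one name.

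A reader might infer that the power calculation or the significance test is also faulty. Neither is: the sample size reproduces, and no effect means a ratio of 1 on every scale. An odds ratio reported as such would be correct. The defect is confined to the size and meaning of the reported percentage, which is the estimate for a primary aim.

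**What to change.** Define the protective effect once in the Data Analysis section, in one of two ways:

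- 1 minus an adjusted risk ratio, from modified Poisson regression with robust variance or from standardised risks based on the logistic model already planned; or
- 1 minus the hazard ratio from the Cox model already planned.

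The first targets the reduction in the risk of any episode. The second targets the reduction in the hazard of a first event. They differ slightly, as steps 4 and 5 of the working show, so only one should carry the name. Any odds ratio should be reported as an odds ratio, described as a reduction in odds.

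The cost is a line or two of text and at most one extra model on the same data. Sample size and data collection do not change. The downside is that the reported percentage becomes slightly smaller.
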